## **6 PROTOCOL COMPLIANCE**

### **6.1 Measures to Ensure Protocol Compliance**

Compliance of the study/reference product prescription scheme with the protocol should be assured by adherence to the preparation rules, compliance with the dosing scheme, and the correct inhalation technique, described in sections 5.2, 5.5, 5.6, respectively.

### **6.2 Patient Compliance**

Compliance with the Investigator's recommendations for the prescribed study/reference product will be checked by the Investigator during discussion with the patient at visits, as well as during the visits regarding the accounting of the returned ampoules of the study/reference product and based on records made in the Patient Diary.

## **7 CONCOMITANT THERAPY, PROHIBITED MEDICATIONS AND THERAPY METHODS**

### **7.1 Concomitant Therapy**

During the study, it is allowed to use drugs for the treatment of concomitant diseases that are not related to prohibited concomitant therapy. All therapies, including drug-free methods that patients received during 30 days prior to enrollment into the study and during the study, should be registered in the relevant sections of the Case Report Form (CRF). The information on the patient's concomitant therapy during the study will be recorded in the CRF.

It is necessary to indicate at least the following: international nonproprietary name and trade name of the medicinal product, route of administration, doses, treatment regimen, and indications.

### **7.2 Prohibited Medicinal Products**

Unauthorized medicinal product groups include:

- Any vaccines
- Any unregistered medicinal products or experimental therapy

### **7.3 Prohibited Therapy Methods**

Prohibited therapy methods include:

- Blood and blood component transfusion– Major surgical interventions (performed under anesthesia and/or in hospital settings)

## 8 EXAMINATION PLAN AND VISITS

### 8.1 Patient Enrollment

A patient of legal age is considered enrolled into the clinical study after he/she has consented to participate by signing and putting a date on the Informed Consent Form and the Patient Information Leaflet. Immediately after obtaining informed consent, the Investigator will provide the patient with filled out Compulsory Life and Health Insurance Policy of the patient participating in clinical studies of medicinal preparation certifying the patient's insurance during the entire study period.

### 8.2 Visit 1. Screening/Enrollment to Study (Days -21 to -1)

Examination of a patient during the Screening period is carried out for his/her qualification for the study. The Screening period will last up to 21 days. The patients meeting the inclusion criteria based on the examination results during the Screening period will be enrolled in the study.

**The Screening Visit involves the following procedures:**

- Procedure for informed consent obtaining
- Collecting demographics, life history, medical history
- Physical examination
- Measurement of vital signs (BP, HR, RR, t°)
- Anthropometry (body weight and height measurement) (*the height is measured once only at the Screening*)
- Quality of life assessment according to St. George's Respiratory Questionnaire (version 2.2.)
- ECG
- Spirometry (*assessment of baseline FEV1*)\*
- Complete blood count
- Biochemical blood analysis
- Sweat test (*if there is a documented confirmation of cystic fibrosis diagnosis, this test is not required*)
- DNA probe assay to detect mutations in CFTR gene (*if there is a documented confirmation of cystic fibrosis diagnosis, this test is not required*)

- Blood test for antibodies to human immunodeficiency virus (HIV) — HIV1 and HIV2 (*results obtained not later than 30 days prior to the Screening Visit are suitable*)
- Blood test for viral hepatitis markers: surface hepatitis B antigen, hepatitis C antibodies (*results obtained no later than 30 days prior to the Screening Visit are suitable*)
- Blood test for anti-drug antibodies (IgG, IgE) to dornase alfa, including neutralizing activity
- Urinalysis
- Pregnancy test — urine test for chorionic gonadotropin with a test-strip (*for women with preserved childbearing potential*)
- Registration of the concomitant therapy
- Evaluation of compliance with inclusion/exclusion criteria

\* The quality of the Screening Visit spirometry findings will be assessed centrally by a certified functional diagnostics specialist who has no access to the patient's personal data, medical history, or information on clinical manifestations of the disease. The FEV1 value obtained from the spirometry of the Screening Visit will be the baseline for the assessment of efficacy parameters.

In the case of ambiguous or doubtful laboratory test results, repeat testing (retesting) can be carried out in agreement with the Sponsor or its representative.

Patients who do not meet all the inclusion/exclusion criteria will not be enrolled in the study. Patients not enrolled in the study due to controlled conditions may be re-screened in agreement with the Sponsor or its representative.

If a patient meets all inclusion/exclusion criteria, he/she will be invited to the study center to undergo the randomization and start the study therapy (Visit 2. Day 1). In this case, the patient will be warned that prior to his/her visit to the study center at Day 1 (Visit 2) he/she should not use Pulmozyme® that is administered as part of the standard medical service.

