Another study involved a retrospective analysis of the medical record data of 112 pediatric patients with a verified cystic fibrosis diagnosis. [40] Sixty-eight of whom were at the age of 3 months to 5 years. Clinical examination and special studies were performed for 1 year. The children used dornase alfa for at least 6 months. The mean age of dornase alfa therapy initiation was 3.2 months; 2 children started the treatment at the age of 1.5 months. The reference group (44 patients) consisted of children at the age of 2 years and older. During trial treatment with the medicinal product in 68 enrolled patients under the age of 5, 33 patients experienced the following adverse events: pharyngitis, laryngitis, rhinorrhea, hyperthermia, bronchospasm. The patients with adverse events underwent symptomatic therapy for 5–10 days; the existing symptoms were reversed and did not require discontinuation of the medicinal product. All adverse events were observed at the beginning of the trial treatment with dornase alfa, during the first 2 weeks of therapy. No other adverse events were revealed during the long-term use of the medicinal product. All patients completed the study; no long-term effects of product inhalations were revealed. Thus, the use of dornase alfa throughout the study was characterized by its good tolerability. Earlier A.Yu. Voronkova reported adverse effects in 29.34% of CF patients. Moreover, 8.8% of patients had to discontinue the medicinal product due to irreversibility of the severe symptoms. [7] According to the study data, discontinuation of medicinal product dornase alfa was required only in 2 cases of 112 (1.8%) medical records analyzed.

Incidence of adverse drug reactions is indicated according to the following classification: very common ( $\geq 1/10$ ), common ( $\geq 1/100$ ,  $< 1/10$ ), uncommon ( $\geq 1/1,000$ ,  $< 1/100$ ), rare ( $\geq 1/10,000$ ,  $< 1/1,000$ ), very rare ( $< 1/10,000$ ), unknown (impossible to estimate from the available data).

**Adverse reactions** associated with the dornase alfa treatment are rare ( $< 1/1,000$ ); in most cases, they are mild, of a temporary character, and do not require dose adjustment.

*Eye disorders:* conjunctivitis.

*Respiratory, thoracic, and mediastinal disorders:* voice change, dyspnea, pharyngitis, laryngitis, rhinitis (all of them of non-infectious nature), respiratory infections, including the infections caused by *Pseudomonas*, increased bronchial secretion.

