#### 3.2 Study Methodology

This study is open-label, prospective, multicenter, randomized, comparative, and parallel-arm.

According to the Screening results, , the patients who meet the inclusion criteria and are without the exclusion criteria will be randomized 1:1 to one of the treatment groups.

**Group I** is an active treatment group (50 patients), administered the medicinal product Tigerase (GENERIUM JSC, Russia) at a dose of 2.5 mg, once a day by inhalation for 24 weeks  $\pm$  1 week.

**Group II** is a reference group (50 patients), administered the medicinal product Pulmozyme® (F. Hoffmann-La Roche Ltd., Switzerland) at a dose of 2.5 mg, once a day by inhalation for 24 weeks  $\pm$  1 week.

An additional study of DNase sputum concentrations will include 24 patients from among the randomized patients (12 patients in Group I treated with Tigerase and 12 patients in Group II treated with Pulmozyme®). The DNase sputum concentration will be assessed once before the first inhalation and twice after the first inhalation of the study/reference product.

During the treatment, patients will be advised to continue the combined therapy that they received before enrollment to the study, including kinesiotherapy.

All patients enrolled in the study undergo the following successive **study periods**:

- **Screening/enrollment in the study** — for 21 days before the first administration of the study/reference product (3 weeks, Days from -21 to -1).
- **Randomization (Day 1)** — confirmed inclusion/exclusion criteria and patient allocation to one of 2 groups of therapy with a unique randomization number.
- **Therapy** — administration of the study/reference product for  $24 \pm 1$  weeks.

The duration of participation of each patient in the study, including the Screening period, will be about 28 weeks.

Upon the study completion, a final report containing the data on all patients enrolled in the study will be submitted to the regulatory authority in due course.

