## 9 TREATMENT PERIOD

### 9.1 Visit 2. Day 1. Randomization (Week 0)

A procedure of randomization will be performed at Visit 2. A unique randomization number will be assigned to each patient. Group I patients will receive the investigational product Tigerase, Group II patients — the reference product Pulmozyme®.

During participation in the study, the patients receiving Pulmozyme® as part of their standard medical service will be provided by the Sponsor with either investigational product Tigerase or reference product Pulmozyme® according to the randomization results.

At Visit 2, the following study procedures will be carried out:

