### **10.1 Collection of Demographics and Medical History**

During the screening, after signing of the Informed Consent Form, the following demographics and medical history data will be collected from all patients:

- Patient's age (date of birth), sex, race;
- Information on the underlying medical condition — the time of onset of the first symptoms, date of diagnosis establishment; report on physical and instrumental examination findings, including the genotype test results and results of the test for chloride level in the sweat gland secretion;
- Information on the treatment of the underlying medical condition — all prior therapy, including drug-free treatment of CF within 1 year before the Screening, including the earlier applied therapies indicating at least the international nonproprietary and trade names of the medicinal product, route of administration, dosing schedules, course of treatment, and indications;
- Information on the previous and current diseases, including surgeries within 1 year before the Screening;
- Administration of medications, currently and within 4 weeks before the Screening Visit;
- Immunization history (within 1 year before the Screening Visit);
- History of allergies;
- Presence/absence of complaints as of the examination date.

At subsequent visits, the following is assessed:

- Presence/absence of complaints;
- Collection of information about AEs from the previous visit;
- Collection of information about concomitant conditions and medications from the previous visit.

When signing the informed consent, all women (with preserved childbearing potential) and men should also provide consent for observing the adequate contraception methods throughout the study. In this study, adequate contraception methods should be considered the use of methods described in Section 4.2.

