## **10.8 Spirometry**

Pulmonary function test (spirometry) will be performed according to the Study Procedure Schedule (APPENDIX 1. Study Procedure Schedule) at the Screening Visit, on Day  $7 \pm 2$  days, Day  $56 \pm 7$  days, Day  $112 \pm 7$  days, and Day  $168 \pm 7$  days in accordance with the standard procedure described in the Guidelines for Conducting of Spirometry.

The quality of spirometry results obtained at the Screening Visit will be assessed centrally by a certified functional diagnostics specialist who has no access to the patient's personal data, medical history, or information on clinical manifestations of the disease. The results of the spirometry performed at the Screening, centrally assessed, and approved, will be used as baseline values.

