### **Analysis of the primary efficacy endpoint**

When analyzing the primary efficacy endpoint (the change in FEV1 at Week 24  $\pm$  1 week from baseline), the data distribution will be preliminarily tested for normality using the Shapiro–Wilk test, as well as a test for symmetry and kurtosis. In the case of a normal distribution, the intergroup comparison will be performed using a t-test. If there are significant deviations from the normal distribution ( $p < 0.05$ ), a non-parametric Mann–Whitney test will be used. The null hypothesis for the equality of the FEV1 change on Week 24  $\pm$  1 week compared to the baseline between the two groups will be tested with a two-tailed test at a significance level of 0.05 using the Stata14 program. In addition, a 95% confidence interval will be calculated for the difference between the two groups. In addition, the generalized linear model (GLM) including sex, patient age, and medical history as covariates may be used to test the influence of different factors.

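### Prior dornase alfa use determines what FEV1 change from a Screening baseline means, but the stated primary test takes no account of it

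*Protocol*

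**What the plan says.** **Who may enrol.** Section 9.1 deals with current Pulmozyme users: those who take it "as part of their standard medical service will be provided by the Sponsor with either investigational product Tigerase or reference product", depending on the arm to which they are allocated. No criterion in Sections 4.1 or 4.2 requires or excludes prior dornase alfa. The nearest is the hypersensitivity exclusion. Both kinds of patient are thus permitted, and no expected proportion is given.

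**Baseline.** Section 8.2 says of FEV1 that the "value obtained from the spirometry of the Screening Visit will be the baseline for the assessment of efficacy parameters". Section 10.8 repeats this: "The results of the spirometry performed at the Screening, centrally assessed, and approved, will be used as baseline values". Screening runs from Day -21 to Day -1. Neither Section 9.1 nor Appendix 1 schedules spirometry at Visit 2.

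**Instruction on Pulmozyme.** It is given once eligibility is confirmed, so after the Screening spirometry: "prior to his/her visit to the study center at Day 1 (Visit 2) he/she should not use" Pulmozyme. The text does not say whether this means the morning of Day 1 or the whole interval since Screening. No pause before Screening is mentioned.

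**Randomisation and analysis.** Section 3.2.1.1 stratifies by baseline FEV1 only. Section 15.1 sets a t-test, or a Mann–Whitney test if normality fails, on the FEV1 change. It adds an optional generalised linear model "including sex, patient age, and medical history as covariates may be used to test the influence of different factors". Neither the Poisson covariates in Section 15.1 nor the Cox covariates in the Protocol Summary name prior dornase alfa.

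**Data available.** Section 10.1 collects "all prior therapy, including drug-free treatment of CF within 1 year before the Screening".

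**The concern.** For a patient who already takes Pulmozyme, the Screening FEV1 contains the drug effect, because nothing in the protocol asks for a pause beforehand. The 24-week change then shows whether the effect is maintained, or what a switch of product does. For a patient who starts dornase alfa on Day 1, the same variable shows onset of effect. The analysis pools the two.

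Three things are at stake. The mean change within an arm cannot be read without knowing how many were already on drug. The rate of reactions that appear on starting treatment depends on the same share. And the primary test leaves out a baseline variable that is likely to predict the outcome and is already in the data. These bear on objective 1 (effect on lung function) and objective 6 (safety of Tigerase).

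**Working it through.** **Inputs from the protocol.** 100 randomised 1:1, so 50 per arm; SD of FEV1 change 10; two-sided alpha 0.05; power 80% (Sections 3.2 and 15.2). Section 1.3.3 gives an average FEV1 gain of 5.8% with long-term use. In a retrospective paediatric series it reports adverse events in 33 of 68 children under 5.

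**Assumptions.** The share of users p is not in the documents: 30–70% is used, and 0–100% for within-arm change. Users change by 0. New starters gain d = 5.8, read as points of % predicted, with half of that (2.9) as the lower end.

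**1. The plan's own figure.** Detectable difference = sqrt(4 × (1.96 + 0.84)² × 10² / 100) = 5.6, as in Table 3. The formula in Section 15.2 prints a squared difference on the left, but the table follows this version.

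**2. Expected change within an arm, identical products.** (1 − p) × 5.8:

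| Users | Mean change |
|---|---|
| 0% | 5.8 |
| 25% | 4.35 |
| 50% | 2.9 |
| 75% | 1.45 |
| 100% | 0 |

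At 30% and 70% users it is 4.1 and 1.7.

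**3. Is the between-arm difference affected?** Take a test product with no effect and a reference worth 5.8 points, with additive effects. Simulating 4,000 trials per setting gives:

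| Users | Test-arm change | Between-arm difference |
|---|---|---|
| 0% | 0.02 | 5.75 |
| 50% | -2.91 | 5.87 |
| 100% | -5.79 | 5.79 |

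The within-arm change moves with the mix, while the contrast does not.

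**4. Variance due to the mix.** p(1 − p)d²:
- Low: 0.3 × 0.7 × 2.9² = 1.8.
- High: 0.5 × 0.5 × 5.8² = 8.4.

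Against a variance of 100 this is 2–8%. Removing it by adjustment cuts the standard error by 1 − sqrt(1 − 0.018) = 0.9% to 1 − sqrt(1 − 0.084) = 4.3%, or about 1–4%.

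**5. Chance imbalance in prior use.** SD = sqrt(2p(1 − p)/50) = 0.092 to 0.100. The shift at the 95% limit is 1.96 × SD × d, from 1.96 × 0.092 × 2.9 = 0.5 to 1.96 × 0.100 × 5.8 = 1.1 points. The unadjusted standard error is 10 × sqrt(2/50) = 2.0, with a confidence half-width of 1.96 × 2.0 = 3.9. The shift is part of that error and does not come on top of it.

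**6. Start-up adverse events, extreme case.** If users have no start-up events and new starters have the paediatric rate of 33/68 = 48.5%, the rate is 24.3% with 50% users and 12.1% with 75%. Power to see a 1.5-fold excess at 50 per arm then falls from 71% to 26% and 13%. Both inputs are assumptions for this trial.

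**The case against.** The strongest reply is that the trial compares two arms, and prior use is fixed before randomisation. It is therefore balanced in expectation, and the primary contrast does not rest on within-arm change. This stands. A reader might infer that the FEV1 comparison is biased, but the documents do not support that.

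It can also be said that the mix inflates the variance beyond the plan. Section 15.2 gives SD 10 as expected for this endpoint, so the mix may already lie within it. Even if it came on top, the SD would be sqrt(108.4) = 10.41 and the detectable difference 5.8 instead of 5.6. The loss is small either way. If nearly all patients are users, or nearly none, it vanishes. With the +2.5 points of % predicted that Section 1.3.3 reports at Year 1 in a treated registry group, and half of the patients users, the mix is 0.25 × 2.5² = 1.6% of the variance.

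On safety, a reader might infer that the adverse event rate is uninterpretable. That goes too far. Of the paediatric series the protocol says "All adverse events were observed at the beginning of the trial treatment with dornase alfa, during the first 2 weeks of therapy", but those were children under 5 and this trial enrols adults. Events here are collected over 24 weeks and include exacerbations (Section 10.5), which are not start-up reactions. Any dilution falls on both arms. It remains true that users given Tigerase knowingly change product while users given Pulmozyme do not.

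Finally, the optional medical-history covariate could be read to cover prior therapy, the Poisson covariate list is left open, and Section 15.3 leaves detail to an analysis plan that is not shown. This stands as a limit, but none of these texts commits to the adjustment, and the primary test as written is unadjusted.

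**Conclusion.** The point holds in a limited form. Current users are admitted, new starters are not excluded, and the users' baseline precedes any instruction to withhold Pulmozyme. The 24-week change therefore mixes maintenance or switching with onset of effect, in unknown proportions. The consequence is for interpretation: within-arm FEV1 change and start-up event rates need a breakdown by prior use before they can be read. The cost in precision is about 1–4% of the standard error under the assumed shares and gains.

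Randomisation keeps the contrast an unbiased estimate for the patients enrolled. If the difference between products were not the same in users and new starters, it would still be a valid average, but one that depends on the mix, which is a further reason to show both groups. The documents do not establish that untreated patients will enrol in any number. Nor does the case require a new stratification factor, which at 100 patients is a trade-off. What carries the point is that a nearly free improvement on the stated test and tables is available.

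**What to change.** - Derive one variable, dornase alfa use at Screening (yes/no), from the prior-therapy data of Section 10.1.
- Prespecify it as a covariate in the FEV1, FVC and exacerbation models. The t-test and Mann–Whitney test take no covariate, so the FEV1 and FVC comparisons need a linear model with arm and prior use.
- Report FEV1 change and adverse events by arm within users and within new starters, with the number in each. State that change from baseline in users means maintenance.
- Reconcile the Section 8.2 instruction with the Screening baseline, so that all sites read the same period for it. Which period applies is for the sponsor to settle.

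The cost is wording in the protocol and analysis plan, one derived variable from data already collected, one extra covariate, and subgroup tables with small numbers. No new visit or measurement is needed.

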## 9 TREATMENT PERIOD

### 9.1 Visit 2. Day 1. Randomization (Week 0)

A procedure of randomization will be performed at Visit 2. A unique randomization number will be assigned to each patient. Group I patients will receive the investigational product Tigerase, Group II patients — the reference product Pulmozyme®.

During participation in the study, the patients receiving Pulmozyme® as part of their standard medical service will be provided by the Sponsor with either investigational product Tigerase or reference product Pulmozyme® according to the randomization results.

At Visit 2, the following study procedures will be carried out:

